## Abstract

**Introduction:**

‘Real world’ bleeding in patients exposed to different regimens of dual antiplatelet therapy (DAPT) and triple therapy (TT, DAPT plus an anticoagulant) have a clinical and economic impact but have not been previously quantified.

**Methods and analysis:**

We will use linked Clinical Practice Research Datalink (CPRD) and Hospital Episode Statistics (HES) data to assemble populations eligible for three ‘target trials’ in patient groups: percutaneous coronary intervention (PCI); coronary artery bypass grafting (CABG); conservatively managed (medication only) acute coronary syndrome (ACS). Patients ≥18 years old will be eligible if, in CPRD records, they have: ≥1 year of data before the index event; no prescription for DAPT or anticoagulants in the preceding 3 months; a prescription for aspirin or DAPT within 2 months after discharge from the index event. The primary outcome will be any bleeding event (CPRD or HES) up to 12 months after the index event. We will estimate adjusted HR for time to first bleeding event comparing: aspirin and clopidogrel (reference) versus aspirin and prasugrel or aspirin and ticagrelor after PCI; and aspirin (reference) versus aspirin and clopidogrel after CABG and ACS. We will describe rates of bleeding in patients prescribed TT (DAPT plus an anticoagulant). Potential confounders will be identified systematically using literature review, semistructured interviews with clinicians and a short survey of clinicians. We will conduct sensitivity analyses addressing the robustness of results to the study’s main limitation—that we will not be able to identify the intervention group for patients whose bleeding event occurs before a DAPT prescription in CPRD.

**Ethics and dissemination:**

This protocol was approved by the Independent Scientific Advisory Committee for the UK Medicines and Healthcare Products Regulatory Agency Database Research (protocol 16_126R) and the South West Cornwall and Plymouth Research Ethics Committee (17/SW/0092). The findings will be presented in peer-reviewed journals, lay summaries and briefing papers to commissioners/other stakeholders.

**Trial registration number:**

76607611; Pre-results.

Strengths and limitations of this studyWe designed our study using the framework recommended by the Cochrane Bias and Non-Randomised Studies Methods Groups for establishing appropriate patient populations, interventions and follow-up to emulate three hypothetical randomised controlled trials (target trials).We will identify potential confounders systematically using literature review, semistructured interviews with clinicians (cardiologists, cardiac surgeons and general practitioners) and a short survey with an additional group of clinicians.Because there are no medication data in Hospital Episode Statistics, we will assume that patients’ first dual antiplatelet therapy (DAPT) prescription that appears in Clinical Practice Research Datalink (CPRD) after their hospital admission is what they were prescribed at discharge.We will conduct sensitivity analyses to address the robustness of results to different assumptions about the unknown intervention group in patients who died or had a bleeding event before a DAPT prescription in CPRD.

## Introduction

Dual antiplatelet therapy (DAPT), a combination of aspirin and either clopidogrel, prasugrel or ticagrelor, is recommended for secondary prevention of ischaemic events (heart attack and stroke) in people with coronary artery disease. Guidelines recommend that patients are treated with DAPT for 6 to 12 months following myocardial infarction (MI) and coronary interventions (percutaneous coronary intervention [PCI] and coronary artery bypass grafting [CABG])^1–3^ and support the use of the more potent antiplatelet inhibitors ticagrelor and prasugrel.^2^ Antiplatelet agents reduce the risk of ischaemic events, by preventing the formation of clots in atherosclerotic coronary arteries and within stents (following PCI) or grafts (following CABG), but increase the risk of bleeding.^4^ Randomised controlled trials (RCTs) have shown that adding clopidogrel to aspirin leads to 1% excess risk of major bleeding (requiring admission to hospital) compared with aspirin alone.^5 6^ Prasugrel and ticagrelor reduce the risk of ischaemic events further but also further increase the risk of bleeding.^7^ Some patients (eg, those with existing atrial fibrillation or those who develop atrial fibrillation after PCI, CABG or acute coronary syndrome [ACS]) are prescribed an anticoagulant (eg, warfarin, dabigatran, rivaroxaban, apixaban) in addition to DAPT (triple therapy [TT]), which further increases the risk of bleeding.

‘Real world’ bleeding events that do not require any intervention are likely to be much more frequent than those reported in RCTs, which excluded patients at high risk of bleeding and mainly reported only on major bleeding. Bleeding events that do not result in hospitalisation are largely managed in primary care and may have a significant clinical and economic impact.^8^ Minor and nuisance bleeding (nose and gum bleeds, bruising and prolonged bleeding from cuts) may also reduce adherence to DAPT^9^ and non-adherent patients may be at increased risk of a secondary ischaemic episode.^10^ Only three studies have reported the incidence and consequences of nuisance bleeding after DAPT^11–13^; these suggest that nuisance bleeding is common (affecting 29%–38% of patients) and impacts on adherence (11% of patients in one study discontinued clopidogrel^12^). A nested case–control study using the Health Improvement Network (a UK primary care database) reported an increased risk of upper gastrointestinal bleeding with clopidogrel and aspirin compared with aspirin alone (relative risk, 2.08; 95% CI 1.34 to 3.21).^14^

The economic impact of bleeding events associated with DAPT is also poorly characterised, in particular for minor bleeding events and their impact on health-related quality of life.^8^ This is not surprising given that health economic analyses often lack detailed data on adverse effects of interventions, despite consensus that such effects should be considered.^15 16^ To ensure appropriate decisions are made about which DAPT regimens to use in clinical practice, the health and resource use consequences of minor and major bleeding events should be incorporated into assessments of cost-effectiveness. For DAPT, this entails accounting for uncertainty in the absolute risk of bleeding, the impact of different bleeding events on health-related quality of life and treatment adherence and subsequent risk of secondary ischaemic events and the cost implications of managing these bleeding events.

We propose to use Hospital Episode Statistics (HES) and the Clinical Practice Research Datalink (CPRD) databases to estimate the incidence of all bleeding events occurring in patients prescribed different DAPT or TT regimens after undergoing coronary interventions (PCI and CABG) and in conservatively managed patients with ACS. Our study will also provide parameter estimates to update existing cost-effectiveness models. We will use the framework recommended by the Cochrane Bias and Non-Randomised Studies Methods Groups for establishing appropriate patient populations, interventions and follow-up to emulate the following three hypothetical RCTs (hereafter referred to as the target trials, table 1)^17^.

**Table 1 T1:** Summary of three target trials and how observational data will be used to emulate these

PICO component	Target trial	Issues in emulating the target trial using observational data
Eligibility criteria	Target trial 1 (PCI) Consecutive patients (age ≥18 years) undergoing PCI (emergency or elective). Exclusions: DAPT or anticoagulant use in the previous 3 months; major bleed requiring hospitalisation in previous 12 months; renal failure requiring dialysis; intolerance/allergy to aspirin, clopidogrel, prasugrel or ticagrelor. Target trial 2 (CABG) Consecutive patients (age ≥18 years) undergoing CABG (urgent and elective). Exclusions: DAPT or anticoagulant use in the previous 3 months; other concomitant cardiac surgery (eg, valve surgery); major bleed requiring hospitalisation in previous 12 months; renal failure requiring dialysis; intolerance/allergy to aspirin, clopidogrel, prasugrel or ticagrelor. Target trial 3 (conservatively managed ACS) Consecutive patients (age ≥18 years) hospitalised for an acute coronary syndrome (ACS): myocardial infarction (MI) with or without ST elevation or unstable angina. Exclusions: PCI or CABG performed at time of ACS diagnosis; major bleed requiring hospitalisation in previous 12 months; renal failure requiring dialysis; intolerance/allergy to aspirin, clopidogrel, prasugrel or ticagrelor.	CPRD-HES linked data set contains information that allows us to identify all eligible patients for the three target trials. The study period is April 2009–July 2017. All eligible patients will have sufficient data (1 year) preceding their index event to apply the exclusion criteria and characterise the population (eg, comorbidities) and sufficient follow-up data (1 year) to identify outcomes. It is not possible to capture intolerance/allergy to aspirin, clopidogrel, prasugrel or ticagrelor.
Interventions	Target trial 1 (PCI) Clopidogrel (75 mg daily) or prasugrel (5 mg or 10 mg daily) or ticagrelor (90 mg twice daily). All patients will receive aspirin (at a dose of 75 mg daily, in line with current guidelines). Target trial 2 (CABG) Clopidogrel (75 mg) in addition to aspirin (at a dose of 75 mg daily, in line with current guidelines) or aspirin only (any dose, reflecting variation in usual care). Target trial 3 (conservatively managed ACS) As for target trial 2.	Relevant interventions can be identified as CPRD has information on all medications (including doses) prescribed in primary care.
Assignment to interventions	Participants are assigned to DAPT interventions in hospital.	Participants enter the study at index procedure date for PCI and CABG, and episode start date for ACS, and will be assigned to DAPT interventions using first prescription in CPRD (within 2 months of hospitalisation) as a proxy for what they were prescribed in hospital (there are no medications data in HES). This assignment will exclude a proportion of eligible patients (those who died or experienced a major bleed that caused them to stop DAPT, or patients who have no prescription for DAPT within the 2-month window); we will identify and describe the characteristics of these excluded patients. In sensitivity analyses, we will address the robustness of results to different assumptions about the intervention group in those patients where the DAPT medication is unknown or a major bleed occurs prior to the first DAPT medication, by using multiple imputation models for handling missing data. Prior known information regarding the likely prescription based on patient characteristics or general policies will be incorporated in these analyses.
Follow-up	Starts at assignment to intervention and ends at first bleed or 12 months from assignment (whichever comes first).	Starts at time of hospitalisation for PCI, CABG or ACS and ends at first bleed or 12 months from hospitalisation (whichever comes first).
Primary outcome	Any bleed within 12 months of the start of DAPT (DAPT is prescribed at hospitalisation for PCI, CABG or ACS).	Any bleed within 12 months of hospitalisation for PCI, CABG or ACS.
Analysis	Intention to treat	According to first prescription for DAPT in CPRD

CABG, coronary artery bypass grafting; CRPD, Clinical Practice Research Datalink; DAPT, dual antiplatelet therapy; HES, Hospital Episode Statistics; PCI, percutaneous coronary intervention; PICO, Population, intervention, comparator, outcome.

In patients who have undergone PCI, estimate the effect on bleeding events of assignment to aspirin and clopidogrel (reference) versus aspirin and prasugrel or aspirin and ticagrelor.In patients who have undergone CABG, estimate the effect on bleeding events of assignment to aspirin (reference) versus aspirin and clopidogrel.In patients who are conservatively managed after presenting with ACS, estimate the effect on bleeding events of assignment to aspirin (reference) versus aspirin and clopidogrel.

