### Study populations

Eligibility and exclusion criteria for the three target trials (for patients undergoing PCI, patients undergoing CABG or patients hospitalised and conservatively managed for ACS) are listed in table 1. We will identify eligible patients who are included in Clinical Practice Research Datalink (CPRD) and eligible for linkage with Hospital Episode Statistics (HES) and Office for National Statistics (ONS) mortality data (because they have a valid NHS number and are registered at a practice that was participating in the linkage programme). Patients are included if they had a PCI, CABG or ACS (index event) record in HES during the study period (1 April 2010–31 January 2017), and have at least 1 year of linked CPRD-HES data before the date of their index event. They must also have been prescribed one of the treatment regimens being compared in the target trial corresponding to their index event. One year’s data preceding eligibility for the target trial is adequate to apply most of the exclusion criteria and determine comorbidities and medication history: such information would be collected at baseline in a randomised trial. The following Office of Population Censuses and Surveys (OPCS) procedure codes (PCI and CABG) and International Classification of Diseases (ICD-10) codes (ACS no procedure) will be used to identify patients: PCI, K49, K50 & K75; CABG, K40, K41, K42, K43, K44, K45 & K46; ACS without a procedure, I20.0, I21, I22, I24.9 (with no OPCS code for PCI or CABG in the same hospital admission). Figure 1 shows full details of the inclusion and exclusion criteria.

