### Triple therapy

We will establish additional groups of patients (PCI or CABG or conservatively managed ACS) based on TT prescription. The main reason for prescribing an anticoagulant is to treat atrial fibrillation in a patient otherwise eligible for either of the three target trials. Atrial fibrillation can precede (long-term anticoagulation for pre-existing atrial fibrillation) or follow the index event (anticoagulation for new-onset atrial fibrillation). Figure 2 shows how the patient groups receiving TT will be constructed.

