**Figure 2 F2:**
[figure not shown]
Study diagram describing the construction of the triple therapy (TT) populations.

We will identify patients on long-term anticoagulation by identifying prescriptions of oral anticoagulants (warfarin, dabigatran, rivaroxaban, apixaban) in the 3 months before their index event and a concomitant prescription of any anticoagulant (TT) with DAPT and in the first 2 months after the index admission. Patients who develop atrial fibrillation after the index event will be identified from any new anticoagulant prescription during follow-up. We have compiled a list of all drug codes in CPRD for antiplatelet agents (aspirin, clopidogrel, prasugrel and ticagrelor) and anticoagulants (warfarin, dabigatran, rivaroxaban, apixaban) (see supplementary appendix 3).

10.1136/bmjopen-2019-029388.supp3Supplementary file 3

In patients receiving various TT regimens (grouped by pre-index event anticoagulant prescription and post-index event anticoagulant prescription in PCI, CABG and ACS separately, see figure 2), we will describe rates of bleeding (number of events/person time) with 95% CIs for each group. We have not specified comparison groups because we know there is large variation in prescribing of anticoagulants; TT is usually prescribed for a relatively short period of time (1–6 months, depending on a patient’s individual risks of thrombosis and bleeding) after which an antiplatelet agent (usually aspirin) is removed and patients continue to receive an anticoagulant and single antiplatelet for the remainder of the 12 months after the index admission.

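### Table 1 leaves the 3-month prior DAPT/anticoagulant exclusion out of the conservatively managed ACS trial, although the abstract applies it to all three cohorts

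*Protocol article*

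**What the plan says.** The abstract (Methods and analysis) names the three patient groups and then gives one set of eligibility conditions for all of them, including "no prescription for DAPT or anticoagulants in the preceding 3 months".

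Table 1 (Eligibility criteria) writes the exclusions out separately for each target trial. The PCI list opens with "Exclusions: DAPT or anticoagulant use in the previous 3 months; major bleed requiring hospitalisation in previous 12 months". The CABG list opens with the same prior-use item. The list for conservatively managed ACS reads "Exclusions: PCI or CABG performed at time of ACS diagnosis; major bleed requiring hospitalisation in previous 12 months; renal failure requiring dialysis" and then ends with drug intolerance or allergy. It has no prior-use item.

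The Study populations section says that the criteria for the three target trials "are listed in table 1", and also that "Figure 1 shows full details of the inclusion and exclusion criteria". Figure 1 is not reproduced in the text available for this review.

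The Triple therapy section adds: "We will establish additional groups of patients (PCI or CABG or conservatively managed ACS) based on TT prescription". Its long-term anticoagulation groups are identified from "prescriptions of oral anticoagulants (warfarin, dabigatran, rivaroxaban, apixaban) in the 3 months before their index event", together with DAPT and an anticoagulant in the first 2 months afterwards.

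**The concern.** The ACS cohort is the largest of the three, and the article gives two different rules for who enters it. The difference concerns exactly the patients whom a target-trial emulation needs to keep out at time zero.

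Patients already taking DAPT have come through an earlier period of exposure, so they are not comparable with patients starting it. Patients on an anticoagulant bleed more when it is combined with DAPT, as the Introduction says. If either group is unevenly spread between aspirin and aspirin/clopidogrel, the bleeding HR absorbs part of that difference. The ACS analysis is also meant to supply event probabilities for cost-effectiveness models.

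**Working it through.** **1. The statements side by side**

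| Place | Prior DAPT/anticoagulant exclusion for ACS? |
|---|---|
| Abstract | Yes, stated once for all groups |
| Table 1, PCI and CABG lists | Stated for those two cohorts |
| Table 1, ACS list | Absent |
| Study populations | Refers to Table 1, and to Figure 1 for full detail |
| Triple therapy | Builds further groups, ACS included, from pre-index anticoagulant use |

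The ACS exclusions are written out in full, so no cross-reference carries the item over from CABG. The Interventions row of the same table does use a cross-reference for ACS. No visible text gives a reason for ACS to differ.

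**2. Who would enter if Table 1 is followed**

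The Interventions section assigns patients by the antiplatelet agents prescribed in the 2-month window and does not look at anticoagulants. Hence:
- prior DAPT users enter the aspirin/clopidogrel arm, or the aspirin arm if only aspirin is prescribed in the window;
- patients on an anticoagulant plus aspirin and clopidogrel enter the aspirin/clopidogrel arm. If they also had the anticoagulant before the index event, they meet the long-term triple-therapy definition ("in the 3 months before their index event and a concomitant prescription of any anticoagulant (TT) with DAPT");
- patients on an anticoagulant plus aspirin alone enter the aspirin arm.

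**3. How large the bias could be**

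The cohort sizes (Sample size section) are ACS 8148 + 3082 = 11,230, PCI 6738 + 842 + 770 = 8350, and CABG 2556 + 595 = 3151.

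The documents give no share of prior users, so what follows is an illustration on assumed inputs. Let pD and pA be the anticoagulated shares in the aspirin/clopidogrel and aspirin arms, and m the multiple of bleeding risk on an anticoagulant. The crude risk ratio is multiplied by

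(1 + pD(m − 1)) / (1 + pA(m − 1)).

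The protocol's assumed rates give a base ratio of 0.09/0.05 = 1.80.

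| pD | pA | m | Factor | Crude ratio |
|---|---|---|---|---|
| 5% | 5% | 2 or 3 | 1.00 | 1.80 |
| 10% | 5% | 2 | 1.10/1.05 = 1.05 | 1.89 |
| 5% | 10% | 2 | 1.05/1.10 = 0.95 | 1.72 |
| 10% | 5% | 3 | 1.20/1.10 = 1.09 | 1.96 |
| 5% | 10% | 3 | 1.10/1.20 = 0.92 | 1.65 |

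The sign depends wholly on the assumed split. The calculation is unadjusted and ignores any separate effect of prior DAPT use.

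**4. What the exclusion would cost in precision**

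The plan's own figures come first. Expected ACS events are 8148 × 0.05 + 3082 × 0.09 = 684.8, against a stated minimum of 680. The detectable HR is

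exp[(z₀.₉₇₅ + z_power) / √(D·p(1 − p)(1 − R²))], with D = 680 and p = 1/3.5.

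At 90% power and R² = 0 this is exp[3.2415/√(680 × 0.2041)] = 1.317, against 1.32 in Table 2. The other five ACS entries also reproduce.

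Now suppose that the exclusion removes a share of ACS patients evenly from both arms, and that the feasibility counts had not already applied it:

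| Share removed (assumed) | Events | HR, 90% power, R² = 0 | HR, 90% power, R² = 0.5 |
|---|---|---|---|
| 0% | 680 | 1.32 | 1.48 |
| 10% | 612 | 1.34 | 1.51 |
| 20% | 544 | 1.36 | 1.55 |
| 30% | 476 | 1.39 | 1.59 |

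The protocol's 9% v 5% implies an HR of ln(0.91)/ln(0.95) = 1.84, which is above every entry.

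**The case against.** The best reply is that this is a one-line slip in a table captioned as a summary. The abstract excludes these patients. The Triple therapy section describes anticoagulated patients as otherwise eligible for the target trials, which suggests that anticoagulation makes them ineligible in all three, and it calls the triple-therapy groups additional. Figure 1, said to hold the full criteria, may list the exclusion for ACS. All of this stands. It means that the documents do not show that prior users will be analysed. It does not remove the conflict between the abstract and Table 1, one of which must be wrong whatever the figure shows.

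A reader might go further and infer three things that the documents do not support:
- **That prevalent users and triple-therapy patients do enter the ACS comparison.** This follows only if Table 1 governs. Triple-therapy patients would then fall in the aspirin/clopidogrel arm, not the aspirin reference arm, because triple therapy includes DAPT by definition.
- **That the HR is inflated.** The direction is unknown, as the illustration shows, and the planned HR is adjusted for systematically identified confounders.
- **That overlap with the triple-therapy groups is itself a bias.** Those groups are described by rates alone, without comparison groups, and the text nowhere says that they are disjoint from the main cohorts.

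**Conclusion.** The eligibility rule for the largest of the three comparisons is contradictory and needs to be reconciled. What is certain is the mismatch: the abstract applies the 3-month prior-use exclusion to ACS, and Table 1, to which the Methods refer for the criteria, does not. The consequence is conditional. If Table 1 is followed, the ACS contrast is not a new-user comparison, and long-term triple-therapy patients on clopidogrel are counted in its aspirin/clopidogrel arm as well as in their own group.

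No bias figure can be taken from the documents. The crude ratios of 1.65 to 1.96 around 1.80 rest on assumed shares of 5–10% per arm and an assumed two- to three-fold risk. They show only that the error could run either way or be nil. The plan's sample-size figures for ACS are not in error.

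**What to change.** Add the 3-month DAPT/anticoagulant exclusion to the target trial 3 list in Table 1, and check that the abstract, Table 1 and Figure 1 then agree. Confirm that the ACS data extraction applies it, and state whether the ACS feasibility counts (8148 and 3082) were made with it in place.

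The text change is one line. The price is a somewhat smaller ACS cohort if the counts did not already exclude these patients. For an assumed 10–30% loss, the detectable HR at 90% power and R² = 0 goes from 1.32 to 1.34–1.39.

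The change does not deal with patients who start an anticoagulant after the index event. A pre-index exclusion cannot remove them, in this cohort or the other two. Nor does it reach prior clopidogrel without aspirin, since the exclusion is worded in terms of DAPT.

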### Interventions

The interventions of interest for the three target trials are shown in table 1. Guidelines recommend low dose aspirin (75 to 100 mg/d) plus either clopidogrel (75 mg/d), prasugrel (5 mg/d or 10 mg/d) or ticagrelor (90 mg twice/d) for PCI and conservatively managed patients with ACS. For PCI patients, the interventions of interest are aspirin and clopidogrel, aspirin and prasugrel and aspirin and ticagrelor. In conservatively managed patients with ACS, clopidogrel is the most commonly prescribed second antiplatelet agent (in addition to aspirin) and a large proportion of patients are prescribed aspirin only; therefore, the interventions of interest are aspirin only (75 to 100 mg/day) and aspirin and clopidogrel. There is variation in aspirin prescription for CABG patients; some surgeons choose 75 mg/day, others 150 mg/day or 300 mg/day. Surgeons may also prescribe an additional antiplatelet agent, most commonly clopidogrel. Therefore, the comparisons of interest in CABG patients are aspirin only (any dose, reflecting variations in usual care in different hospitals) and aspirin and clopidogrel (doses as for PCI). We have specified these comparisons based on preliminary feasibility counts from CPRD, which indicate that few CABG and conservatively managed patients with ACS are prescribed aspirin and prasugrel or aspirin and ticagrelor.

In the target trials, the interventions would be assigned during the hospital stay, as soon as patients are eligible for antiplatelet therapy. Our observational data set does not have information on medication given to patients at discharge, because HES does not include medications data. Therefore, the first time at which we have information on the antiplatelet regimen to which patients were assigned in hospital is when they receive their first primary care prescription/s for aspirin or DAPT, recorded in CPRD. It is reasonable to use these as a proxy for the medications that patients started in hospital, because patients’ general practitioners (GPs) are unlikely to change the prescriptions that were started in hospital.

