### Follow-up

The start of follow-up (the index event) will be the date of the index hospital procedure (PCI, CABG) or start date of the hospital episode that contains the ACS diagnosis (ACS). Patients will be followed up until 12 months after the index event, since DAPT is prescribed for 12 months in accordance to guidelines.

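### In the CABG and ACS comparisons outcome counting can start before the regimen is assigned, so bleeds in the index episode that precede assignment can count as outcomes of a known arm, and no planned analysis removes them

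*Protocol article*

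**What the plan says.** Table 1 has a target-trial column and an emulation column. The target-trial outcome is "Any bleed within 12 months of the start of DAPT", and a bracket in that cell adds the assumption that DAPT is prescribed at hospitalisation. The emulated outcome is "Any bleed within 12 months of hospitalisation for PCI, CABG or ACS". On entry, the same table says: "Participants enter the study at index procedure date for PCI and CABG, and episode start date for ACS". The Follow-up section repeats this: "The start of follow-up (the index event) will be the date of the index hospital procedure (PCI, CABG) or start date of the hospital episode" (for ACS, the one with the qualifying diagnosis).

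The Interventions section places assignment in the target trial later than that: "the interventions would be assigned during the hospital stay, as soon as patients are eligible for antiplatelet therapy". In the data, the arm comes from CPRD prescriptions in a 2-month window, and a patient with aspirin alone in that window goes to the aspirin-only arm.

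The Outcomes section counts all HES and CPRD bleeds during follow-up and makes no exception for the index episode. The prior-bleed exclusion in Table 1 looks back over the previous 12 months. The first sensitivity analysis uses multiple imputation. Table 1 and Interventions say it includes patients whose major bleed came before the first DAPT prescription. Statistical analyses describes it as being for patients with no prescription data.

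**The concern.** In a target trial, only events after assignment can be outcomes of the arm. Here, the clock and the event count can start before assignment. Consider a patient admitted with ACS who also has a presenting bleed, or a CABG patient with operative bleeding on the procedure date, who later gets aspirin alone from the GP. The arm is known, so the patient is in the main analysis, and the bleed is a first event at or near time zero.

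Two consequences follow. Bleeds that the regimen could not have caused are added to both arms and dilute the hazard ratio. If such a bleed also makes clinicians prefer aspirin alone, the outcome helps to determine the arm and the extra events gather in the reference group. Adjusting for baseline confounders does not repair this, because the bleed is the outcome and not a covariate. In a time-to-first-bleed model it also hides any later on-treatment bleed in the same patient. CABG and ACS are the most exposed comparisons because they are the ones with an aspirin-only arm.

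**Working it through.** **Plan's own figures (Sample size section).** Expected events are the sum of patients × rate:
- CABG: 2556 × 0.05 + 595 × 0.09 = 127.8 + 53.6 = 181 (stated: at least 180).
- ACS: 8148 × 0.05 + 3082 × 0.09 = 407.4 + 277.4 = 685 (stated: at least 680).

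The detectable HR is exp[(1.960 + z_power) / √(D·p(1−p))]. CABG with D = 180 and p = 1/5 gives 1.83 at 90% power and 1.69 at 80%. ACS with D = 680 and p = 1/3.5 gives 1.32 and 1.27. All agree with Table 2, so the sample size is not in question.

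**HR implied by the plan's rates.** ln(1 − 0.09) / ln(1 − 0.05) = 0.0943 / 0.0513 = 1.84.

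**Illustration.** Let a share x of the cohort carry a pre-assignment index-episode bleed, and let a fraction s of those patients end on aspirin only. Then:
- aspirin risk = 0.05 + x·N·s / n0
- aspirin/clopidogrel risk = 0.09 + x·N·(1 − s) / n1
- HR = ln(1 − risk1) / ln(1 − risk0)

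Both x and s are assumptions; the documents give neither. "No steering" means the same share x in each arm, which is s = 8148/11,230 = 73% in ACS and 2556/3151 = 81% in CABG. Strong steering is taken as s = 90% (ACS) and 95% (CABG).

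| Cohort | x | No steering: risks | HR | Strong steering: risks | HR |
|---|---|---|---|---|---|
| ACS (N = 11,230) | 1% | 6.0% v 10.0% | 1.70 | 6.2% v 9.4% | 1.53 |
| ACS | 2% | 7.0% v 11.0% | 1.61 | 7.5% v 9.7% | 1.32 |
| CABG (N = 3151) | 1% | 6.0% v 10.0% | 1.70 | 6.2% v 9.3% | 1.53 |
| CABG | 2% | 7.0% v 11.0% | 1.61 | 7.3% v 9.5% | 1.31 |

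Worked line, ACS at x = 2% with s = 90%: 224.6 bleeds, 202.1 to aspirin and 22.5 to aspirin/clopidogrel. The risks are 0.05 + 202.1/8148 = 0.0748 and 0.09 + 22.5/3082 = 0.0973, so HR = 0.1024 / 0.0778 = 1.32. Combining the risks as 1 − (1 − a)(1 − b) instead of adding them changes the HRs by no more than 0.02.

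**Effect on CABG power.** Power = Φ(ln HR × √(D·p(1−p)) − 1.96), with p = 595/3151 and D including the added events (181 + 32 = 213 at x = 1%; 181 + 63 = 244 at x = 2%). It starts at 89%. Without steering it becomes 86% and 83%; with strong steering it becomes 68% and 38%.

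**Do the planned analyses remove these events?** The first sensitivity set imputes a regimen; it does not move time zero or drop the bleed. The second concerns medication changes around bleeds. The third restricts to patients at low bleeding risk but keeps the outcome definition. None starts the count after assignment.

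**The case against.** The protocol states an aligning assumption: the target-trial outcome cell says DAPT is prescribed at hospitalisation. If that held exactly, the two columns would coincide. This deserves credit, but the Interventions section lets assignment fall later in the stay, so the assumption can fail in the patients at issue.

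No sentence says that index-episode codes are outcomes. That follows from the follow-up and outcome rules with no carve-out. Figure 1, which is said to hold the full criteria, and the bleeding code list are not shown here and could contain one. This limit stands. The view that HES bleeding codes cannot be ordered within an episode is likewise an inference from the choice of ACS index date.

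The imputation analysis does mention major bleeds before the first DAPT prescription, so it would be wrong to say the plan ignores them. What it changes, however, is the arm and not the event.

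A reader might infer that these bleeds are known to concentrate in the aspirin arm. The documents do not say so. They speak of a major bleed causing patients to stop DAPT, which makes steering plausible but does not establish its extent.

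A reader might also infer that patients with an index-episode bleed should simply be excluded from the primary analysis. Where treatment began in hospital, such a bleed may be an effect of the regimen, so exclusion would condition on an outcome. The plan itself expects most bleeds soon after the index event. This objection stands and shapes the fix.

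**Conclusion.** The point holds as a gap between time zero and assignment that no planned analysis tests. As written, index-episode bleeds that precede assignment can count as first-bleed outcomes of a known arm in CABG and ACS. If they are unrelated to arm, the HR is diluted; if they influence the choice of aspirin only, it is biased further towards or below 1.

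The documents fix neither the size nor the degree of steering. Under assumed shares of 1–2%, the HR of 1.84 falls to about 1.6–1.7 without steering and about 1.3–1.5 with strong steering. It does not fall below 1 anywhere in that range, so the figures do not support a claim that the result would reverse. That 2% with strong steering in ACS lands on the plan's detectable HR of 1.32 is a result of the chosen inputs and carries no further meaning. The conclusion also assumes that the unseen figure and code list hold no exclusion of index-episode bleeds.

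**What to change.** - Pre-specify, for CABG and ACS and for consistency PCI, an analysis that starts event counting after the index episode ends and does not count index-episode bleeding codes as outcomes.
- Report index-episode bleeds by arm in each cohort, which also shows whether the assumed shares above are realistic.
- State in Table 1 that time zero can precede assignment, and say how index-episode codes are handled. If Figure 1 or the code list already removes them, one sentence there settles the point.
- Interpret the primary HR alongside the added analysis. Do not make exclusion of patients with an index-episode bleed the sole primary analysis.

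The cost is some protocol and analysis-plan wording and one further model run per cohort; the plan already uses HES episode dates. Because the main analysis already requires a prescription after discharge, starting the count at the end of the episode should lose few analysable patients. The drawback is that the added analysis leaves out genuine early on-treatment bleeds in hospital, which is why it should accompany the primary analysis and not replace it.
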